### Randomization

To avoid interference between the intervention and the control groups, stratified randomization will be carried out on the school level (according to the type of school and number of grade 8 classes). Expecting a higher drop-out of schools in the intervention group, randomization follows a 3:2 ratio, that is, each school will have a 3:2 chance of being assigned to the an intervention group. Randomization will be performed with a computer program.

### Data collection

From October 2013 to January 2014 the recruitment and randomization of schools will take place. In the intervention as well as in the control group, baseline data will be obtained in January and February 2014. The intervention program is scheduled for the period of March to May 2014. During this time the control group runs the usual curriculum. After 12 weeks, in the period of June to July 2014, post assessment data will be obtained. The follow-up assessment is planned for June and July 2015.

### Pilot study

The program has been tested, evaluated and adapted during a pilot study. From April to June 2013 a pilot study with a shorter intervention period (eight weeks) was conducted, including two schools with four classes and 89 students (41 female students; M_age_ = 13 years, SD = 0.50 years). To evaluate and improve the “läuft.” physical activity program, different qualitative and quantitative methods were employed: participant observation of the educational lessons, questionnaires for students and teachers to evaluate these lessons, and the assessment as well as interviews with students and teachers about the entire intervention. Based on the insights gained with respect to feasibility, comprehensibility and acceptance from the obtained data and experiences, the program was modified. The intervention was followed by one assessment in order to evaluate the feasibility of physical and medical testing as well as the comprehensibility of the questionnaire. The assessment was adapted in accordance with the experiences and results.

### Measures

The outcomes will be measured anonymously with self-administered questionnaires, physical testing and medical testing on the individual level as well as qualitative methods on the individual and the class level. An overview of all outcomes that will be assessed is presented in Table 1.

**Table 1 T1:** Overview of measures

**Measurement methodology**	**Outcome**
**Medical testing**	Body weight and height (BMI percentiles)
	Body composition (fat mass)
	Waist circumference [35]
	Blood pressure
	Resting heart rate
	Heart rate after stress
	Recovery heart rate
**Physical testing**	Cardiovascular fitness [36]
**Questionnaire**	*Socio*-*demographic characteristics*
	Age
	Gender
	Migration background
	Socio-economic status [37]
	*Lifestyle Behavior*
	Physical activity* [38-40]
	Sedentary behavior [40]
	Use of tobacco [41]
	Use of alcohol [42,43]
	Food pattern [44]
	*Psychological constructs*
	General self-efficacy [45]
	Self-efficacy towards physical exercise [46]
	Self-concept for general physical capacity and physical attractiveness [47,48]
	Enjoyment of physical activity [49]
	Enjoyment of sedentary behavior [49]
	Sensation seeking [50]
	Physical well-being [51]
	Psychological well-being [51]
	Depression [52]
	Intention for physical activity [53]
	*Social factors*
	Parental support for physical activity [25]
	Friends physical activity*
	Normative expectations*
	Environmental situation to be physical active*
**Qualitative methods**	Activating-strategies (group discussion, document analysis)
	Interactive processes (group discussion)

*self-constructed items.

To permit a linking of individual information on subsequent assessments while assuring anonymity, each assessment-booklet will be labeled with a seven-digit individual code generated by the student [54].

#### Medical testing

Standing height will be determined using a portable stadiometer (Seca 213, Basel, Switzerland) and body weight as well as body composition (fat mass) using bioelectrical impedance analysis (Omron BF-511, Omron Healthcare, Mannheim, Germany). Students’ BMI will be calculated and converted into age- and gender-specific percentiles using the Coles LMS-method [55] on the basis of a representative German sample [56]. For further analysis, the standard deviation scores will be determined. Blood pressure and resting heart rate will be measured with an automated oscillometric device (M5-Professional, Omron Healthcare, Mannheim, Germany). A flexible tape will be used to determine waist circumference at the medial axillary line half-way between the lowest rib and the iliac crest [35]. For measuring heart rate after stress as well as recovery heart rate after three minutes, respectively, pulse watches with chest belts will be used (Polar FT1, Polar Electro GmbH, Büttelborn, Germany). The entire medical testing will be conducted under a physician’s supervision.

#### Physical testing

For measuring cardiovascular fitness, the 20-meter shuttle run test will be conducted [36]. In this progressive running test, the students have to run between two lines for a distance of 20 meters. The required running pace of an initial 8.0 km/h increases continuously by 0.5 km/h each minute. Students have to cross the opposite line in a given time interval indicated by prerecorded audio signals. The test stops when the student fails to reach the line by the sound for the second time. To determine aerobic capacity, the number of one-minute stages will be counted with a precision of 0.5 stages. The 20-meter shuttle run test allows a validated estimation of maximal oxygen uptake as an indicator of cardiovascular fitness [57,58].

#### Questionnaire

Data about socio-demographic characteristics, lifestyle behaviors well as psychological and social variables will be collected by self-administered questionnaires. The items and scales used are based on published and validated questionnaires and the international literature. The entire questionnaire was tested for feasibility and comprehensibility during the pilot study with 89 students. Based on the experiences in the pilot study regarding comprehensibility and acceptance of items and conducted item analyses, the questionnaire has been revised and shortened. Considering item analyses, items have been excluded if (a) item difficulty was smaller than 20% and larger than 80%, respectively, (b) item-rest correlation was smaller than .40 and (c) their exclusion either led to higher internal consistencies or did not substantially decrease internal consistency of the particular scale.

Table 2 summarizes item characteristics and internal consistencies of the scales that have been modified based on the results of the pilot study and that will be employed in the planned study. Furthermore, for self-constructed items and scales seven-day retest-reliabilities were determined on a subsample of 38 students.

**Table 2 T2:** Item characteristics and internal consistencies of modified scales in their final version

		**Pilot study ****(N = ****89)**		
**Scales**	**Number of Items**	**Cronbach’****s α**	**Item**-**rest correlation**	**Item difficulty ****(in%)**
General self-efficacy	5	.83	.58 to .66	60.8 to 68.2
Self-concept: general physical capacity	5	.92	.78 to .83	50.6 to 70.5
Self-concept: physical attractiveness	5	.84	.58 to .71	57.9 to 76.1
Sensation seeking	2	.86		41.0, 43.6
Self-efficacy for physical activity	8	.87	.56 to .78	42.9 to 70.5
Physical activity enjoyment	10	.92	.58 to .85	53.9 to 75.6
Sedentary behavior enjoyment (screen-based)*	4			
Sedentary behavior enjoyment (non-screen-based)	4	.89	.57 to .84	54.2 to 66.4
Parental support for physical activity	2	.79		31.3, 34.8
Psychological well-being	5	.80	.46 to .72	55.3 to 74.4
Physical well-being	2	.70		59.8, 66.1

*In the pilot questionnaire there were two separated scales for TV/DVD time and computer use. Both scales will be combined as overall screen-based sedentary behavior. Hence, there are no item characteristics available for this combined scale.

##### Socio-demographic characteristics

Socio-demographic characteristics like school type, age, gender and migration background will be assessed as well as the socio-economic status asking for the parents’ highest educational attainment [37].

##### Lifestyle behavior

Adapted items of the MoMo-activity-questionnaire [38] will be used to assess physical activity in different contexts (school, sports clubs and leisure time) and in different dimensions (duration, frequency and intensity) as well as the mode of commuting to school. These questions provide information about physical activity during a regular week. Besides, students in the pilot study were asked with which activities they choose to spend their recess time in school. The three activities that were named the most (sitting or standing while talking to others, walking through the school or schoolyard, and sports such as football or basketball) will be included in the final questionnaire. Students will be asked how often they engaged in these activities during the recess times of the last week. Overall moderate to vigorous physical activity will be determined by a reliable and validated two-item screening measure [39]. The survey method for leisure time sedentary behavior was modified from Zabinski and colleagues [40]. Students will be asked how much time they spent on the most recent school day and the most recent Sunday with different sedentary behaviors. Different physical activities were added to the list providing insights into the distribution of sedentary and active leisure time during a specific day. The list of activities is based on the original questionnaire, categories for physical activity (active transport, household activities, physical activity in sports clubs, in school and in leisure time), and extended by answers of students in the pilot study. Lifetime smoking and current smoking [41] as well as lifetime alcohol use, current alcohol use and frequency/number of previous binge drinking [42,43] will be assessed. Finally, students will be asked how often they consume different foodstuff in a usual week, namely, fresh fruits and vegetables, sweets or chocolate, soft drinks, fast food and water [44] (retest-reliability (r) ranged from 0.39 to 0.63).

##### Psychological variables

Items of published and validated scales selected with respect to item analysis during the pilot study will be used for the assessment of general self-efficacy [45], self-efficacy towards physical activity [46], physical self-concept for general physical capacity and physical attractiveness [47,48], enjoyment of physical activity PACES (Physical Activity Enjoyment Scale) [49], sensation seeking [50] as well as physical and psychological well-being [51]. The enjoyment of screen-based and non-screen-based sedentary behaviors will be assessed with four adapted items of the PACES [49] (non-screen-based sedentary behavior: r = .59). The scale “depressed affect” of the German version of the Center for Epidemiological Studies Depression Scale for Children CES-DC [52,59] and three items to assess the intention for physical activity were added to the questionnaire after the pilot study. Thus, students will be asked how much they agree with three given statements, (for example: “I plan to be physically active for at least 60 minutes per day on most days of the next week.”; seven-point semantic differential scale from “likely” to “unlikely”) [53].

##### Social variables

Parental support for physical activity will be assessed by an adapted version of a scale used by Trost *et al*. [25] (r = .80). Furthermore, students will be asked how many of their friends are physically active regularly (5-point scale: “none” to “all”, r = .72), how many are in a sports’ club (5-point scale: “none” to “all”, r = .69), how important it is in their circle of friends to be physically active (4-point scale: “not important” to “very important”, r = .50) and how often their parents were physically active without them in the past week (5-point scale: “never” to “more than five times”, r = .78). Two items will be used to obtain information about the environmental situation to be physically active: “In my neighborhood there are many facilities in which for being physically active.” (5-point scale: “strongly disagree” to “strongly agree”, r = .60) and “When I want to do sports, facilities and equipment are lacking.” (5-point scale: “never” to “always”, r = .70). Finally, normative expectations of physical activity and screen time will be assessed. Therefore, students will be asked for their estimation of the portion of adolescents that are physically active for 60 minutes on a daily basis (r = .60) and how many hours per day adolescents spend watching TV or on the computer (r = .61).

#### Qualitative methods

In addition to and in combination with quantitative methods, a qualitative analysis of processes and outcomes of the “läuft.” program will be performed. During the program, document analyses of students’ entries on the homepage will be conducted. Group discussions with students will be carried out in the course of the post-assessment.

##### Document analysis

To gain insights into processes of the intervention immediately, a qualitative document analysis of activities on the “läuft.” homepage will be conducted. The homepage can be used by students to take part in the creativity contest, compete with their amount of steps, share their individual experiences in the program, discuss program associated topics and participate in weekly tasks. Students’ activities and entries on the homepage will provide information about the activating-strategies that will be used and developed during the intervention.

##### Group discussion (students’ perspective)

In order to obtain a deeper understanding of students’ experiences, motives and interpretations of given impulses and activating-strategies during the program, group discussions with selected members of each intervention class will be conducted in the course of the post-assessment. On the basis of a theoretical sampling [60], five to seven students differing with regard to (a) gender, (b) interest in and commitment to the “läuft.” program and (c) athleticism will be asked to participate in the group discussions. These will follow a thematic compendium and will be carried out in accordance with the principles of Bohnsack [61], which emphasize the self-deployment of the group and the minor impact of the researcher on group processes.

### Process evaluation

To evaluate the quality of implementation, teachers will be asked to fill in questionnaires about the realization of each intervention component during the program. Information about acceptance, feasibility and suggestions for improving the program will be provided by another questionnaire for all participating teachers after the intervention and interviews with selected teachers. The latter will additionally enable a more profound and case-oriented analysis of interaction processes, barriers and success strategies. The teachers will be selected using theoretical sampling based on results of the questionnaires as well as formal criteria (for example, gender and type of school).

### Statistical analysis

Statistical analysis will be conducted with Stata V13.1 (Stata Corp, College Station, TX, USA) following the intention to treat principle. To evaluate efficacy of the program, multilevel analysis with the levels: schools, classes, individuals and waves, will be performed. Random intercepts will be included for schools, classes and individuals taking the clustering effect into account. Group and covariates will be taken as fixed effects. Differences between intervention and control group at baseline as well as attrition analysis will be examined using a t-test for independent samples and Fisher’s exact test.

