### Study design

The effectiveness of the “läuft.” physical activity program will be tested in a two-arm three-wave cluster randomized controlled trial. Data of the different waves are hypothesized to be clustered at the individual, class and school level. Schools are the units of randomization and will be randomly allocated to the intervention and control group. In intervention schools the “läuft.” physical activity program will be implemented, while schools of the control group run through the usual curriculum and will receive no further intervention. In both groups, fitness, medical and questionnaire data will be collected for three times: “baseline” (immediately before the intervention), “post” (immediately after the intervention) and “follow-up” (12 months after the end of the intervention) assessment. In addition, after the intervention, qualitative analyses will be conducted in classes of the intervention group to gain insight into interactive processes within the classes and to reconstruct subjective experiences and interpretations of activating-strategies.

Process evaluation of the planned trial will be realized through questionnaires and interviews during and after the study, respectively. The study design is presented in Figure 2.

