### Sample size calculation

There are specific constraints for analysis of cluster randomized trials [26] since the responses of individuals within a cluster tend to be more similar than those of individuals of different clusters. This clustering effect can be defined as 1 + (m-1)p, where m is the average number of subjects per cluster and p the intraclass correlation coefficient (ICC) [27]. The ICC for physical fitness and adiposity was taken from another cluster randomized controlled trial, the Kindersportstudie (KISS) [28,29] and estimated with approximately 0.05 (p). Assuming an equal average cluster size of 20 pupils with parental consent (m = 20), a clustering effect of 1.95 was determined. Without taking into account the clustering of the data, assuming a small to medium effect size of the intervention (Cohen’s d = 0.30) on physical activity as one primary and the most important outcome being still detectable at follow-up, applying a significance level of alpha = 0.05 and power = 0.80, it can be estimated that N = 350 pupils are required to detect a difference between two independent sample means [30,31]. Taking the cluster effect into account, a required sample size of N = 683 students and 34 classes was determined. A computerized sample size calculator for cluster randomized trials was used to confirm this estimation [32].

Based on earlier experiences [33,34], a drop-out rate of 25% over the study was hypothesized. Hence, a total sample size of 911 pupils and 46 classes will be recruited for baseline to detect possible differences between the groups at follow-up. In order to recruit the estimated sample size of 46 classes while assuming a participation rate of 20% and an average of at least two participating classes per school, about 100 schools will be invited to participate.

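### Baseline and attrition comparisons are planned with tests that ignore clustering; at the planning ICC a nominal 5% test between arms has a true error of about 16%

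*Protocol article*

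**What the plan says.** Four parts of the protocol article bear on this.

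- **Statistical analysis**, on the descriptive comparisons: "Differences between intervention and control group at baseline as well as attrition analysis will be examined using a t-test for independent samples". The same sentence names Fisher's exact test as well. No allowance for clustering and no school- or class-level summary is mentioned for these comparisons.
- **Statistical analysis**, on the efficacy model, shortly before that sentence: "Random intercepts will be included for schools, classes and individuals taking the clustering effect into account".
- **Study design**: "Schools are the units of randomization and will be randomly allocated to the intervention and control group", and "Data of the different waves are hypothesized to be clustered at the individual, class and school level". The Randomization section confirms that "stratified randomization will be carried out on the school level". It also gives the reason for the 3:2 ratio: more intervention schools than control schools are expected to be lost.
- **Sample size calculation**: it notes that the "responses of individuals within a cluster tend to be more similar than those of individuals of different clusters". It takes an ICC of about 0.05 from another school trial's fitness and adiposity data, assumes 20 pupils per class, and arrives at a clustering effect of 1.95.

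**The concern.** An independent-samples t-test and Fisher's exact test both get their standard error or reference distribution from independent pupils. Here whole schools are allocated, so pupils in one school share both an arm and whatever makes them alike. The effective sample is smaller than the head count, and the unadjusted p-value is too small. The plan recognises this for the sample size and for the efficacy model, but not in the sentence on baseline differences and attrition.

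What is at stake is the credibility of two reported results: whether the arms were comparable at baseline, and whether loss to follow-up was selective. The second matters in this trial, because 25% drop-out is assumed and part of it is expected to be the loss of whole schools. Chance differences between schools could then be reported as imbalance or selective attrition.

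**Working it through.** **Inputs from the Sample size calculation section:** d = 0.30, alpha = 0.05 (sidedness not stated; two-sided reproduces the plan's N), power 0.80, ICC 0.05, 20 pupils per class, at least two classes per school on average, 25% drop-out, 911 pupils in 46 classes. Derived: 46 / 2 = 23 schools of about 2 × 20 = 40 pupils.

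**1. The plan's own chain.**
- Unclustered: 2 × (1.96 + 0.84)² / 0.30² gives 175 per arm after rounding up, so 350. Matches.
- Design effect: 1 + (20 − 1) × 0.05 = 1.95. Matches.
- Clustered: 350 × 1.95 = 682.5, so 683 pupils, or about 34 classes. Matches.
- With drop-out: 683 / 0.75 = 910.7, so 911; 911 / 20 = 45.6, so 46 classes. Matches.

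**2. True error of an unadjusted two-sided 5% test between arms.** If the variance of the arm difference is DE times what the test assumes, the error is 2 × (1 − Φ(1.96 / √DE)).

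| Where the ICC of 0.05 sits | DE | 1.96/√DE | True error |
|---|---|---|---|
| Class only (the protocol's figure) | 1.95 | 1.404 | 16.0% |
| Half school, half class (derived) | 1 + 19 × 0.05 + 20 × 0.025 = 2.45 | 1.252 | 21% |
| School only (derived) | 1 + 39 × 0.05 = 2.95 | 1.141 | 25.4% |

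**3. Check by simulation** (arms split about 3:2, no true difference).
- t-test, 23 schools × 2 classes × 20 pupils: 15.2%, 20.5% and 25.9% for the three rows above.
- Fisher's exact test, 25% event rate, ICC 0.05: 16.5% with 46 clusters of 20, and 25.0% with 23 clusters of 40. With an ICC of zero it gave about 4%, so the excess comes from clustering.

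**4. Sensitivity to the ICC** (values other than 0.05 are assumptions).

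| ICC | Clusters of 20 | Clusters of 40 |
|---|---|---|
| 0.01 | 7.2% | 9.6% |
| 0.02 | 9.5% | 14.2% |
| 0.05 | 16.0% | 25.4% |
| 0.10 | 25.0% | 37.6% |

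**5. Drop-outs against retained pupils on a baseline variable.** This is another natural meaning of an attrition analysis, and it behaves differently because drop-outs and retained pupils can come from the same school. Simulated with 23 schools of 40, baseline ICC 0.05 and 25% drop-out:

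| ICC of drop-out itself (assumed) | Error of the t-test |
|---|---|
| 0 | 5.1% |
| 0.05 | 5.4% |
| 0.3 | 11.9% |
| 0.8 | 20.8% |

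This comparison goes wrong only when drop-out is strongly concentrated by school.

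**The case against.** The best defence is that these are descriptive checks and that the efficacy analysis handles clustering properly. That stands, and it limits the harm. Several stronger readings are tempting, and the document does not support them.

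- **That false differences will be declared three to five times too often.** The multiples are 16.0/5 = 3.2 and 25.4/5 = 5.1, but only at an ICC of 0.05. The protocol gives that value for fitness and adiposity alone, and states only the design effect of 1.95. Applying it to all measures in Table 1 to predict a count of false positives would assign the same ICC to age, gender, food pattern and the psychological scales, for which no ICC is given. Stratifying by school type and number of grade 8 classes may also lower the inflation, by an amount that cannot be worked out from the text.
- **That attrition results are always affected, and worse than baseline.** Step 5 shows an error near 5% when drop-out is individual or weakly clustered. For attrition by arm, the plan itself anticipates a real difference in school loss, so a small p-value there need not be a false positive, although it would still overstate the evidence.
- **That the tests will choose the covariates or distort the efficacy result.** Nothing in the Statistical analysis section links them to covariate choice or to the efficacy model.
- **That baseline tests are pointless in any randomised trial.** Schools are randomised before baseline data are collected. The Procedure section leaves open whether parental consent follows allocation. If it does, consent could differ by arm, and a cluster-adjusted baseline comparison could be informative.

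It might also be said that a condensed article leaves such detail to a fuller plan. That does not answer the point: the article names the tests, and the tests named do not fit the design.

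**Conclusion.** The point holds in limited form. The stated tests conflict with the protocol's own account of its data. For pupil-level comparisons between arms, a nominal 5% test has a true error of about 16% at the planning ICC and class size. It could reach about 25% if all of that ICC is between schools of about 40 pupils, and it falls to about 7% to 14% at assumed ICCs of 0.01 to 0.02. For drop-outs against retained pupils, the error is inflated (about 12% to 21% in the cases simulated) only if drop-out is strongly clustered, which the expected loss of whole schools makes possible.

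These figures assume that the tests are run on individual pupils, which is the natural reading since no cluster-level summary is mentioned, and that stratification does not remove much between-school variance. The damage is confined to the reported baseline balance and attrition results. It should be corrected, but it does not put the efficacy analysis in question.

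**What to change.** Replace the one sentence in the Statistical analysis section so that:

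1. baseline balance is described by arm, with summaries and standardised differences, and any significance test is cluster-adjusted;
2. attrition is compared with a multilevel logistic model with random intercepts for school and class, or a cluster-robust equivalent;
3. the number of schools lost is reported for each arm. If drop-out is mainly by whole schools, this count says more than a pupil-level p-value.

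The cost is a sentence of text and a few extra model runs. The multilevel framework is already planned for the efficacy analysis, and neither the data collection nor the sample size changes.
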